### **2.3 BENEFIT - RISK ASSESSMENT**

The overall safety profile outlined in [Section 1.2](#) is favourable for human studies at chronic doses up to 50 mg/day. The maximum dose administered in the single rising dose study was 800 mg and the maximum dose for a 4 week treatment was 100 mg/day and both regimes

Proprietary confidential information.

© 2012 Boehringer Ingelheim International GmbH or one or more of its affiliated companies. All rights reserved.

This document may not - in full or in part - be passed on, reproduced, published or otherwise used without prior written permission.

were well tolerated. In Phase II, 12-week treatment duration Trials 1245.9 and 1245.10 in T2DM subjects, the maximum daily dose of BI 10773 was 50 mg. All doses of BI 10773 were well tolerated in these studies.

Because of the insulin-independent mechanism of action of BI 10773 and in light of the fact that GFR is physiologically decreased during episodes of hypoglycaemia (due to reduced renal blood flow hence leading to lowering of UGE and therefore efficacy of BI 10773), the risk of hypoglycaemic episodes with BI 10773 alone is considered to be low. A daily dose of 25 mg BI 10773 has been previously shown to result in urinary excretion of nearly 80 g of glucose every 24 hours. Hence, to adjust the daily insulin requirements in anticipation of the observed increased glucosuria, study subjects will be required to reduce their bolus insulin injections based on Table 2.3: 1 (below); this measure further limits the potential for hypoglycaemia to occur. The estimates for the anticipated required reduction in the amount of bolus insulin doses at the start of treatment (Day 3) are based on the 500 Rule (for Humalog or NovoLog) or the 450 rule (for regular insulin). As an added safety measure, subjects will also be required to decrease their insulin basal dose by 30% at the start of treatment in order to potentially prevent the possible risk of nocturnal hypoglycaemia (based on Table 2.3: 2). If subjects are on a different basal to bolus breakdown than the below examples, the correct reduction amount of basal and bolus insulin will be determined by the investigator.

Table 2.3: 1 Percent reduction in the amount of each daily bolus insulin injection to account for the daily urinary excretion of 80 grams of sugar

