| Total Daily Insulin Dose (TDD) In Units | The 500 Rule: Grams of Carbs Covered by 1 Unit of Humalog | Units of insulin needed to cover 80 grams of sugar | % reduction in amount of daily bolus insulin to account for 80g urinary sugar excretion per below basal to bolus breakdowns |                        |                        | The 450 Rule: Grams of Carb Covered by 1 Unit of Regular | Units of insulin needed to cover 80 grams of sugar | % reduction in amount of daily bolus insulin to account for 80g urinary sugar excretion per below basal to bolus breakdowns |                        |                        |     |
|-----------------------------------------|-----------------------------------------------------------|----------------------------------------------------|-----------------------------------------------------------------------------------------------------------------------------|------------------------|------------------------|----------------------------------------------------------|----------------------------------------------------|-----------------------------------------------------------------------------------------------------------------------------|------------------------|------------------------|-----|
|                                         |                                                           |                                                    | 40% Basal
60% Bolus                                                                                                      | 45% Basal
55% Bolus | 50% Basal
50% Bolus |                                                          |                                                    | 40% Basal
60% Bolus                                                                                                      | 45% Basal
55% Bolus | 50% Basal
50% Bolus |     |

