#### 4.2.1 Rescue medication, emergency procedures and additional treatments

During the screening and run-in period, subjects should continue to take the antidiabetic treatment they were receiving at informed consent as background therapy. The background insulin medication can remain unchanged or change partially or completely as per subject needs or based on the investigator's clinical judgement (treatment to target according to local guidelines is encouraged).

Insulin will not be provided as part of the clinical trial supplies.

To prevent the possible risk of hypoglycaemic episodes in subjects with T1DM on insulin therapy and BI10773, study subjects will initially be required to reduce their basal and bolus insulin injections by approximately 30% at the start of the treatment phase (one day after Visit 4 – study Day 3). All subjects must follow an appropriate investigator-recommended carbohydrate counting method and insulin titration algorithm during the course of the study in order to achieve optimal and individualized glycaemic goals. It is expected that insulin requirements will change during the course of the treatment phase and as such, each subject will have to titrate their insulin intake accordingly to prevent episodes of hyper or hypoglycaemia. Insulin dose adjustments should be done when feasible under the investigator's guidance. In addition, subject will have to test their blood glucose level at home several times a day as recommended by the investigator. Any insulin dose change or adjustment must be based on blood glucose measurements (not CGM data).

In case of hypoglycaemia, which may put a subject at risk (for example, repeated symptomatic hypoglycaemia or severe hypoglycaemia), appropriate reduction of ongoing background therapy (insulin) should be initiated in consultation with the investigator when feasible.

There are no special emergency procedures to be followed. There are no rescue medications in this trial. The patient's background insulin dose can change at any time in order to achieve the best standard of care.

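### Table 2.3: 1 contradicts itself: the 450-Rule units column disagrees with the grams-per-unit and percent columns in all seven rows, by up to about 7.7-fold

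*Protocol*

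**What the plan says.** Section 2.3 of the Protocol starts from a daily "urinary excretion of nearly 80 g of glucose every 24 hours" at the trial dose. To limit hypoglycaemia it then states that "study subjects will be required to reduce their bolus insulin injections based on Table 2.3: 1 (below"). The same section places this "required reduction in the amount of bolus insulin doses at the start of treatment (Day 3"), and uses the 500 Rule for Humalog or NovoLog and the 450 rule for regular insulin.

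Table 2.3: 1 has one half for each rule. Each half runs from left to right:
- grams of carbohydrate covered by one unit, headed "The 500 Rule: Grams of Carbs Covered by 1 Unit of Humalog" or "The 450 Rule: Grams of Carb Covered by 1 Unit of Regular";
- "Units of insulin needed to cover 80 grams of sugar";
- three percent columns, for bolus shares of 60%, 55% and 50%, described as the "reduction in amount of daily bolus insulin to account for 80g urinary sugar excretion per below basal to bolus breakdowns".

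For any other basal-to-bolus split, Section 2.3 leaves the amount to the investigator. Section 4.2.1 separately requires subjects to "reduce their basal and bolus insulin injections by approximately 30% at the start of the treatment phase".

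**The concern.** The three column groups form a chain: grams per unit give units, and units give percentages. In the 450-Rule half, grams per unit fall from 23 to 8 as TDD rises from 20 to 60, so the units that cover a fixed 80 g must rise. The printed units fall, from 4.0 to 1.3, while the percentages in the same rows stay at 28% to 36%. These columns cannot all be true together.

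The table is mandatory and is meant as a hypoglycaemia safeguard in subjects with type 1 diabetes. Anyone who works from the units column reaches a different bolus reduction from someone who works from the percent columns. From TDD 25 upward the units column gives the smaller reduction, and the difference grows with the dose.

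**Working it through.** **Inputs**, all from Section 2.3: 80 g of sugar; the printed grams per unit, units and percentages in Table 2.3: 1; bolus shares of 60%, 55% and 50%.

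**Formulas**, from the column headings:
- units = 80 / (grams per unit)
- percent = 100 × units / (TDD × bolus share)

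**Control: the 500-Rule half.** For TDD 20, 25, 30, 35, 40, 50 and 60, 80 divided by the printed 25, 20, 17, 14, 13, 10 and 8 g/unit gives 3.2, 4.0, 4.7, 5.7, 6.2, 8.0 and 10.0. These are the printed units. All 21 percentages also reproduce to rounding, so the formulas are the ones the table uses.

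**The 450-Rule half.** The percentages below are for the 60% bolus share.

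| TDD | Printed g/unit | 80 / g per unit | Printed units | 80 / TDD | Ratio, 80/g to printed | % from 80/g | Printed % | % from printed units |
|---|---|---|---|---|---|---|---|---|
| 20 | 23 | 3.48 | 4.0 | 4.00 | 0.87 | 29.0 | 29 | 33.3 |
| 25 | 18 | 4.44 | 3.2 | 3.20 | 1.39 | 29.6 | 30 | 21.3 |
| 30 | 15 | 5.33 | 2.7 | 2.67 | 1.98 | 29.6 | 30 | 15.0 |
| 35 | 13 | 6.15 | 2.3 | 2.29 | 2.68 | 29.3 | 29 | 11.0 |
| 40 | 11 | 7.27 | 2.0 | 2.00 | 3.64 | 30.3 | 30 | 8.3 |
| 50 | 9 | 8.89 | 1.6 | 1.60 | 5.56 | 29.6 | 30 | 5.3 |
| 60 | 8 | 10.00 | 1.3 | 1.33 | 7.69 | 27.8 | 28 | 3.6 |

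Four results follow.

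1. All 21 printed 450-Rule percentages (the seven shown and those for the 55% and 50% shares) reproduce from the printed grams per unit. None of the seven printed units does.
2. All seven printed units equal 80/TDD to one decimal. The column matches division by the total daily dose instead of by the grams per unit. Neither rounding nor damage to the table in text extraction would give that pattern in every row.
3. Working back from the printed percentages at TDD 60 gives 0.28 × 36 = 10.1, 0.30 × 33 = 9.9 and 0.33 × 30 = 9.9 units, not 1.3. At TDD 20 it gives about 3.5, not 4.0.
4. At TDD 60 both halves print 8 g/unit and 28/30/33%, yet one prints 10.0 units and the other 1.3.

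**Size at TDD 60.** From the printed figures the ratio is 10.0 / 1.3 = 7.7. It is 7.5 if 1.3 is taken as 80/60 = 1.333, and 8.2 with unrounded grams per unit (450/60 = 7.5; 80/7.5 = 10.67; 10.67/1.3).

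**A split the table does not list (assumed for illustration).** Take TDD 60 with a 45% bolus share, so 27 bolus units. The printed 1.3 units are 1.3/27, about 5% of the bolus. The 10.0 units implied by the grams column are 10.0/27, about 37%.

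**Basal insulin.** Table 2.3: 2 reproduces in full from TDD × basal share × 0.70. The conflict concerns the bolus table only.

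**The case against.** The strongest reply is that the units column is an intermediate step and not the instruction. The table's title announces a percentage cut to each bolus injection, and its summary row averages percentages only. Nothing in the Protocol tells anyone to subtract the units figure from an injection. The percentages agree with the grams column and broadly with the approximately 30% of Section 4.2.1, so an implied cut of 4% or 8% would look odd next to them. This stands, and it is the main limit on the consequence.

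The 450 Rule also applies only to regular insulin. Inclusion criterion 6 (Section 3.3.2) admits multiple daily injections of any type of insulin, so such subjects may enter, but the Protocol gives no number. This stands as well.

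The reply does not remove the contradiction. For a split outside the three listed, no percent column applies and the investigator determines the amount. The units column is then the only figure in the table for the reduction itself that does not depend on the split, which makes it a natural starting point. Section 4.2.1 does not resolve this either, because it is one more figure with which the units column disagrees.

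A reader might infer that the insulin-requirement and hypoglycaemia endpoints are compromised. The Protocol does not support that. Those endpoints are summarised descriptively (Sections 7.3.2.2 and 7.3.3). Insulin is re-titrated throughout on blood glucose readings (Section 4.2.1), and subjects are contacted daily on Days 3 to 7 (Section 6.2.2). The primary analysis concerns GFR under clamped glycaemia about eight weeks later.

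**Conclusion.** The 450-Rule units column is wrong as written, in the sense that it contradicts its own heading and the columns on either side in all seven rows. Relative to those columns the printed units are somewhat high at TDD 20 (4.0 against 3.5) and too low from TDD 25 upward, reaching 1.3 against 10.0 at TDD 60. With a 60% bolus share, the units read literally imply a cut of about 8% at TDD 40 and about 4% at TDD 60, against the printed 30% and 28%.

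This rests only on figures printed in the table. The practical exposure rests on one condition that the Protocol neither directs nor prevents: that someone works from the units for a subject on regular insulin.

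Two stronger readings go too far. One is that the required percentage reduction is itself miscalculated: the percentages in both halves reproduce. The other is that every subject's Day 3 reduction is affected: the 500-Rule half and Table 2.3: 2 are arithmetically sound. What remains is a safety-relevant contradiction in a mandatory insulin table, with an effect on endpoints possible but not shown. Nothing here says which insulin reduction is clinically right.

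**What to change.** The clinical team should reconcile the 450-Rule units column of Table 2.3: 1 with the grams-per-unit and percent columns in the same rows, and with the approximately 30% in Section 4.2.1, then re-issue the table to the site. Until that is done, the site should be told in writing that the units column conflicts with the rest of the table. No dose is proposed.

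The cost is one column of seven cells, carried in an amendment or clarification letter. No design, sample-size or analysis element changes.

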- I. During the screening, treatment and follow up periods, several daily measurements of plasma glucose are recommended including a fasted daily measurement and additional daily measurements including before and after meals and at bedtime. Unscheduled measurements must always be done in cases of hypo- or hyperglycaemia-related symptoms. All HBGM results will be captured in a subject study diary. Treatment decisions must always be based on blood glucose values as determined by using a home blood glucose meter.
- J. Four specific periods of 8-point HBGM will be conducted and results will be recorded by the subject at home in a specific HBGM 8-point log. The 8-point weighted mean daily glucose (MDG) profile must be performed 1 day after Visit 2 and Visit 14 and one day prior to Visits 8 and 11 (thus subjects should start the 8-point test in the mornings of study days -13, 28, 49 and 66). The 8 points of measurements will be: (#1) after a 10 hour fast before study drug intake and 0-5 mins prior to intake of breakfast, (#2) 90 mins after breakfast, (#3) 0-5 mins prior to intake of lunch, (#4) 90 mins after lunch, (#5) 0-5 mins prior to intake of dinner, (#6) 90 mins after dinner, (#7) 0-5 mins prior to bedtime and (#8) after a 10 hour fast before study drug intake and 0-5 mins prior to intake of breakfast (the next day).
- K. Collection of safety / efficacy labs and PK samples will be done based on the attached table, also listed in [Section 5.2.3](#). For Visit 15, if required, other panels/tests may be repeated (fasted measurements as needed) based on clinically significant findings at Visits 11-13 or per investigator judgment.

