| 20                                                     | 5.6                                                                                                                                    | 6.3                    | 7.0                    |
| 25                                                     | 7.0                                                                                                                                    | 7.9                    | 8.8                    |
| 30                                                     | 8.4                                                                                                                                    | 9.5                    | 10.5                   |
| 35                                                     | 9.8                                                                                                                                    | 11.0                   | 12.3                   |
| 40                                                     | 11.2                                                                                                                                   | 12.6                   | 14.0                   |
| 50                                                     | 14.0                                                                                                                                   | 15.8                   | 17.5                   |
| 60                                                     | 16.8                                                                                                                                   | 18.9                   | 21.0                   |

As CGM will be used in all subjects, a hypoglycaemia threshold alarm will be programmed in all CGM devices (for example 2.2 mmol/l) to prompt subjects to intervene by adjusting their insulin level in case needed or by eating carbohydrates should their glucose level fall to unsafe levels. All treatment decisions must always be based on confirmed blood glucose levels as determined by fingerstick readings using a home blood glucose meter.

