## 5.2 SAFETY

### 5.2.1 Endpoints of safety

- Incidence of adverse events

Proprietary confidential information.

© 2012 Boehringer Ingelheim International GmbH or one or more of its affiliated companies. All rights reserved.

This document may not - in full or in part - be passed on, reproduced, published or otherwise used without prior written permission.

- Protocol-specified significant adverse events
- Hypoglycaemic events: Occurrence of serious hypoglycaemia, symptomatic hypoglycaemia (mild or moderate) and time spent in CGM defined hypoglycaemia
- Hypoglycaemic events or time spent in CGM-defined hypoglycaemia day vs. night
- Change in frequency of asymptomatic hypoglycaemia <3.0 mmol/l (by home blood glucose monitoring) from baseline
- Change in weight from baseline
- Change in waist circumference
- Changes from baseline in clinical laboratory values (e.g. electrolytes)
- Vital signs

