#### Criteria for hypoglycaemic events

Every episode of plasma glucose below or equal to 70 mg/dl (3.9 mmol/l) should be documented in the eCRF with the respective time and date of occurrence. Any hypoglycaemia with glucose values  $< 54$  mg/dl ( $< 3.0$  mmol/l) and all symptomatic and severe hypoglycaemias should be documented as an AE "hypoglycaemic event".

For the analysis, all hypoglycaemias will be classified according to the following criteria:

- Asymptomatic hypoglycaemia: Event not accompanied by typical symptoms of hypoglycaemia but with a measured plasma glucose concentration  $\leq 70$  mg/dl (3.9 mmol/l)
- Documented symptomatic hypoglycaemia with glucose concentration  $\geq 54$  mg/dl and  $\leq 70$  mg/dl ( $\geq 3.0$  mmol/l and  $\leq 3.9$  mmol/l): Event accompanied by typical symptoms of hypoglycaemia
- Documented symptomatic hypoglycaemia with glucose concentration  $< 54$  mg/dl ( $< 3.0$  mmol/l): Event accompanied by typical symptoms of hypoglycaemia but no need for external assistance
- Severe hypoglycaemic episode: Event requiring the assistance of another person to actively administer carbohydrate, glucagon or other resuscitative actions.

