### 5.3.2 Other assessments

#### 5.3.2.1 Home Blood Glucose Monitoring (HBGM)

All subjects will be provided with equipment for HBGM and supplies for use at home during the study. Instructions on proper HBGM, using a supplied BG meter, will be provided by the study staff. The subject will be asked to record the results of HBGM on supplied study HBGM logs (in a study subject diary) which will be included in the subject source document files. Only in the case of linked adverse events or of hypoglycaemia, the single value from HBGM will be recorded in the eCRF (except for the specific 8-point HBGM).

During the trial, HBGM should be performed multiple times daily as recommended by the Investigator or at any time the subject is symptomatic, i.e., experiences signs/symptoms of hyper- or hypoglycaemia. If during the trial after an overnight fast, a test result from HBGM reveals blood glucose of >13.3 mmol/l (>240 mg/dl) or <3.9 mmol/l (<70 mg/dl), the subject when feasible should contact the site immediately. The investigator should then instruct the subject to titrate their insulin regimen in order to adequately control their hyperglycaemia or hypoglycaemia. *All insulin treatment decisions must be based on blood glucose values measured using a home blood glucose meter or based on lab values obtained through the local laboratory.*

Proprietary confidential information.

© 2012 Boehringer Ingelheim International GmbH or one or more of its affiliated companies. All rights reserved.

This document may not - in full or in part - be passed on, reproduced, published or otherwise used without prior written permission.

The same blood glucose meter system will be supplied to all subjects and must be used by all subjects during the course of the study. In addition to routine daily measurements, an 8-point HBGM will be done 1 day after Visit 2 and Visit 14 and one day prior to Visits 8 and 11 (thus subjects should start the 8-point test in the mornings of study days -13, 28, 49 and 66).

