#### 5.3.2.2 Continuous Glucose Monitoring (CGM) Evaluation

Participants will use CGM to obtain unbiased glucose data in order to determine to what extent the administration of BI10773 as adjunctive-to-insulin in T1DM alters diurnal glycaemic patterns. Specifically, diurnal glucose exposure, variability and stability will be measured and compared within groups during the baseline period and other time points during the study treatment and follow up periods (example: first 2 weeks of treatment, 2 weeks in the middle of the treatment period, 2 last weeks of the treatment period and the post-treatment period). Changes between baseline and each study period for other parameters of glycemic variability (examples, MAGE: mean amplitude of glycaemic excursions, SD: standard deviation) will be characterized.

All subjects will be instructed to properly use the Guardian® REAL-Time Continuous Glucose Monitoring System (supplied by Medtronic of Canada Inc.). This device is commercially available with single-use disposable electrochemical sensing elements. The Guardian® REAL-Time Continuous Glucose Monitoring System allows glucose levels to be recorded for up to six days at a time (after which a sensor change is required for additional continued monitoring). Subjects will be trained to insert the sensor and perform recommended daily calibrations. Initially, and if applicable, each new glucose sensor must be calibrated after the 2-hour warm-up period, and again within 6 hours. After that, meter blood glucose values must be linked to the Guardian® system as required for proper calibration if applicable (twice daily or as needed). Subjects will be reminded that all treatment decisions must be based on meter blood glucose values (taken several times daily) not glucose values displayed through the CGM. Study subjects will be instructed to replace the sensor every 6 days in order to capture continuous glucose monitoring from (study day -14 to study day 72) and to verify proper sensor self-insertion and daily calibration as required.

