The change from baseline to end of study in the measurement of the inter-quartile range (IQR, mg/dL), a continuous CGM variability marker, will be an ~~important~~ exploratory parameter. Other exploratory AGP glycaemia endpoints involve comparisons between treatment groups for measurements of glucose exposure (area under the median interstitial glucose curve [AUC, mg/dL/24hr]) and glucose stability (pooled rate of change in the median curve, average moment-to-moment change in interstitial glucose, mg/dL/hr), % time in hyperglycaemia (>180 mg/dL or >10 mmol/l), % time in hypoglycaemia (<60 mg/dL or <3.3 mmol/l) and proportion of CGM readings within 70-140 mg/dL (3.9-7.8 mmol/l). Additional glycaemia measures include MAGE and average durations of the hyperglycaemic and hypoglycaemic episodes, mean values from HBGM and changes in the proportion of subjects within clinical target categories. Parameter changes from the baseline to end of study will be analyzed within the group.

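### The only CGM low-glucose alarm level the protocol offers, an example of 2.2 mmol/l, sits below every level at which the protocol itself treats glucose as low, and no floor is set

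*Protocol*

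**What the plan says.** Section 2.3 presents the CGM alarm as one of the measures that keep the hypoglycaemia risk acceptable: "a hypoglycaemia threshold alarm will be programmed in all CGM devices (for example 2.2 mmol/l) to prompt subjects to intervene". The prompt is meant to make the subject adjust insulin or eat carbohydrate when glucose becomes unsafe. The level is an example, not a requirement. The protocol names no other alarm level and no lowest permitted setting. The CGM set-up text in section 5.3.2.2, section 6.2.1 and Flow Chart footnote B covers sensor insertion, calibration and replacement but does not mention the alarm.

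Elsewhere the protocol fixes several levels at which glucose counts as low:

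- **CGM analysis (section 7.3.2.2):** one of the exploratory measures is the percentage of "time in hypoglycaemia (<60 mg/dL or <3.3 mmol/l".
- **Adverse events (section 5.2.3, criteria for hypoglycaemic events):** values under 54 mg/dl, that is under 3.0 "mmol/l) and all symptomatic and severe hypoglycaemias should be documented as an AE". The same section has every value at or below 3.9 mmol/l entered in the eCRF.
- **Safety endpoint (section 5.2.1):** "Change in frequency of asymptomatic hypoglycaemia <3.0 mmol/l (by home blood glucose monitoring) from baseline".
- **Site contact (section 5.3.2.1):** if an overnight-fasted meter reading "reveals blood glucose of >13.3 mmol/l (>240 mg/dl) or <3.9 mmol/l (<70 mg/dl), the subject when feasible should contact the site immediately".

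Section 2.3 also names the night as a specific concern. Subjects must "decrease their insulin basal dose by 30% at the start of treatment in order to potentially prevent the possible risk of nocturnal hypoglycaemia".

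**The concern.** An alarm exists to warn before or as glucose becomes dangerous. At 2.2 mmol/l it would sound only after glucose had already passed the level for contacting the site, the level that defines CGM hypoglycaemia and the level recorded as an adverse event. The only number given to site staff is therefore one that the rest of the protocol would treat as well past the point of concern.

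What is at stake is the low that nobody feels or sees: an asymptomatic episode, or one during sleep. The protocol takes both seriously. It classifies asymptomatic lows, makes them a safety endpoint, and cites nocturnal hypoglycaemia as the reason for cutting basal insulin. For these episodes the alarm is the safeguard best placed to act, because it needs neither symptoms nor an awake subject. With the example setting, such a low between 2.2 and 3.3 mmol/l would trigger no threshold prompt.

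**Working it through.** The protocol gives no derivation for 2.2 mmol/l, so there is no calculation to reproduce. The check compares the example with each low-glucose level in the protocol.

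**Step 1: units.** The protocol's own pairs give the conversion factor: 54/3.0 = 18.0, 60/3.3 = 18.2 and 70/3.9 = 17.9 mg/dL per mmol/l. Applied to the example, 2.2 mmol/l is 39.5 to 40.0 mg/dL, or about 40 mg/dL.

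**Step 2: gaps.** Gap = level − 2.2; relative gap = gap / level.

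| Level (mmol/l) | Where it stands | Measured by | Gap (mmol/l) | Relative gap | Gap (mg/dL, about) |
|---|---|---|---|---|---|
| 3.0 | 5.2.3 (adverse event); 5.2.1 (endpoint) | plasma or meter | 3.0 − 2.2 = 0.8 | 0.8/3.0 = 27% | 54 − 40 = 14 |
| 3.3 | 7.3.2.2 (time in hypoglycaemia) | CGM | 3.3 − 2.2 = 1.1 | 1.1/3.3 = 33% | 60 − 40 = 20 |
| 3.9 | 5.3.2.1 (fasting, site contact); 5.2.3 (eCRF record) | plasma or meter | 3.9 − 2.2 = 1.7 | 1.7/3.9 = 44% | 70 − 40 = 30 |

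The example is below all of them. Only the 3.3 mmol/l comparison is like for like, since both it and the alarm refer to the CGM reading. The other two are blood levels.

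**Step 3: what else would catch a low between 2.2 and 3.3 mmol/l.**

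- *Meter tests.* Flow Chart footnote I recommends several readings a day (fasted, around meals, at bedtime) and adds: "Unscheduled measurements must always be done in cases of hypo- or hyperglycaemia-related symptoms". These cover waking hours and symptomatic lows. No test is scheduled during sleep.
- *Insulin reduction.* Basal and bolus doses are cut by about 30% at Day 3 (section 4.2.1). This lowers the risk at the start, but insulin is then titrated to individual goals.
- *Calls.* Contact is daily on Days 3-7 (section 6.2.2); after that, telephone contact is weekly.
- *Exclusions.* Hypoglycaemia unawareness is excluded on investigator judgement (section 3.3.3). That lowers the risk of unfelt lows but does not remove lows during sleep.
- *Visible CGM values.* Section 5.3.2.2 tells subjects to treat on meter readings, "not glucose values displayed through the CGM", so the values are on the screen. That helps only a subject who is awake and looking.

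None of these reliably covers an asymptomatic low during sleep.

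**Step 4: frequency.** The protocol does not say how much time subjects are expected to spend between 2.2 and 3.3 mmol/l, so the number of affected episodes cannot be calculated.

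**The case against.** The strongest reply is that nothing is fixed. The value is an example in a background section, and a site that programs 3.3 or 3.9 mmol/l complies fully. Device set-up is site work, and site instructions may give a level that is not visible here. This stands as a limit on weight. It does not remove the point, because the protocol offers one number, that number is poor, and nothing prevents its use.

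A second reply is that the levels serve different purposes. Recording rules, an analysis cut-off and a site-contact rule are not alarm levels, and an alarm need not equal any of them. That is correct, and there is no formal contradiction. But an alarm meant to prompt action at unsafe glucose is hard to defend when it sits below the level already counted as an adverse event.

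Third, any chosen floor is partly a preference: 3.3 mmol/l is itself below 3.9. This also stands in part. The reason for 3.3 is that it is the protocol's only hypoglycaemia level defined on the CGM signal, and as a floor it leaves the site free to go higher.

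Fourth, section 5.3.2.2 says CGM is worn to obtain unbiased glucose data, and time in CGM-defined hypoglycaemia is a safety endpoint. An alarm at the cut-off may shorten the time measured below it. That is a real trade-off, although the protocol does not give it as the reason for 2.2.

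Finally, the safeguards are broader than those listed above. Brittle diabetes and recent severe hypoglycaemia requiring emergency hospital treatment are also exclusions (section 3.3.3), and repeated episodes can lead to withdrawal (section 3.3.4.1). The device may also have other alerts, on which the protocol is silent. These points lower the risk, but none is an alarm for a sleeping subject.

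**Conclusion.** The point holds as a minor, inexpensive safety improvement. The only stated CGM alarm level is 0.8, 1.1 and 1.7 mmol/l below the protocol's levels of 3.0, 3.3 and 3.9 mmol/l, and no floor is set. The consequence is conditional: it arises only if a site uses the example, and it assumes that no other device alert is active. Its frequency is unknown. Sample size, hypotheses and the primary GFR analysis are untouched, and no bias in any endpoint has been shown.

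**What to change.** In section 2.3, replace the parenthetical example with a minimum: *at no lower than 3.3 mmol/l (60 mg/dL), set at Visit 2*. This takes the protocol's own CGM definition of hypoglycaemia. Because it applies from the start of CGM wear, run-in and treatment share the same minimum. Leave the rule that treatment decisions rest on fingerstick readings as it is: the alarm prompts a check and the meter confirms it. Keeping each subject's setting the same through Visit 15, and dating any change, would be good practice but is optional.

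The cost is one phrase in the protocol and one device setting at Visit 2. Subjects would get more alarms and do more CGM-prompted checks, which may somewhat shorten the measured time below 3.3 mmol/l.
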